##### Professionals

An interview to collect the professional's experience following the implementation of 3D Print tools in their relationship with patients and their entourage will be carried out within the urology department no later than one year after the inclusion of the first patient.

#### 7.6 STOPPING RULES

##### 7.6.1 TERMINATION OF A PERSON'S PARTICIPATION IN RESEARCH

A participant who wishes to abandon or withdraw his or her consent to participate in the research (as he or she is entitled to do at any time) is no longer followed within the framework of the protocol, but must be subject to the best possible care taking into account his or her state of health and the current state of knowledge.

A withdrawal is a decision by an included participant to assert his or her right to interrupt his or her participation in a research study, at any time during the follow-up, without incurring any prejudice as a result and without having to justify himself or herself.

A withdrawal of consent is a decision by a participant to reconsider his or her decision to participate in a research study and to assert his or her right to cancel his or her informed consent, at any time during the follow-up and without incurring any prejudice as a result and without having to justify himself or herself.

The investigator should identify the cause of the dropout/withdrawal and assess whether it is possible to collect the primary endpoint variable at the time of dropout/withdrawal. Dropouts/withdrawals should be promptly notified to the coordinating investigator, sponsor, and methodology and data management center. The reasons and date of dropouts should be documented in the case report and in the participant's medical record.

#### 7.6.2 STOP RESEARCH

End of research or planned termination of research: end of participation of the last person who participates in the research, also called the last visit of the last participant included in the research.

When the research has reached its planned end (planned termination), the end of the research must be declared to the ANSM and the CPP within 90 days.

Early termination of research: clinical research is terminated (definitively) early. This is the case, in particular, when the sponsor decides:

- not to start the research despite obtaining a favorable opinion from a CPP;
- not to resume the research after having temporarily interrupted it or after its suspension by the ANSM.

When the research is terminated (definitively) early, the end of the research must be declared to the ANSM within 15 days, indicating the reasons for this termination. Temporary cessation of research: the temporary cessation of clinical research consists of:

- stopping the inclusion of new people in this research;
- and/or stopping the practice of the acts provided for in the research protocol.

Any decision by the sponsor to temporarily interrupt the research must be the subject of immediate information to the ANSM and the CPP concerned and, in a second stage and within a maximum period of 15 calendar days following the date of this interruption, of a request for authorization of substantial modification concerning this temporary cessation submitted to the ANSM and a request for advice to the CPP concerned.

### 7.7 DEVIATIONS FROM PROTOCOL

Deviations can concern all aspects of a research protocol: inclusion process, monitoring, measurement of judgment criteria, treatments. All must be documented by the investigator and discussed in the Scientific Council.

Only dropouts result in a cessation of monitoring. Even in the event of a deviation from the protocol, the participant's monitoring must be carried out until the end of the period provided for in the protocol.

#### 7.7.1 PREMATURE AND DEFINITIVE TERMINATION OF THE RESEARCH PROCEDURE

Participants who stop prematurely continue to be monitored as planned by the protocol. Under no circumstances should the planned monitoring be modified.

The participant must receive the best possible care given his or her state of health and the current state of knowledge.

#### 7.7.2 LOST TO FOLLOW UP

A participant is considered lost to follow-up when he or she stops the follow-up planned under the protocol for no reason known to the investigator, so that data collection cannot be carried out as planned.

Participants lost to follow-up should be actively sought by the investigator.

### 7.7.3 PARTICIPANT WRONGLY INCLUDED

A participant is considered to be wrongly included when he or she has actually been included in the research while not meeting all the eligibility criteria. Participants wrongly included must be discussed by the Scientific Council. They must continue to be followed as provided for in the protocol until a decision is made by the Scientific Council.

### 7.8 SIMULTANEOUS PARTICIPATION IN OTHER RESEARCH, EXCLUSION PERIOD, COMPENSATION AND REGISTRATION IN THE VRB FILE

Outside of the ACCURATE and ANXIETY studies, the person may participate simultaneously in another research.

No compensation will be received by the participants during the duration of this research.

## 8. MANAGEMENT OF ADVERSE EVENTS / SIDE EFFECTS / INCIDENTS

Adverse events/adverse effects/incidents must be reported to the various health monitoring circuits applicable to each product or practice concerned (care vigilance, pharmacovigilance, haemovigilance, cosmetovigilance, etc.) in accordance with the regulations in force.

Reporters must specify that the patient is included in a clinical trial and precisely identify the clinical trial concerned.

If the investigator becomes aware of a breach of patient safety in the context of the research, he must inform the sponsor without delay.

## 9. STATISTICAL APPROACH

### 9.1 STUDY SIZE

#### Patients

The study approach is mainly of an anthropological type by systemic essence, it is based on a mixed approach with observations, interviews and questionnaires. In order to be able to combine, within the framework of the collection and then the analysis, the qualitative and quantitative approaches it was decided to build a study with 60 patients divided into 2 randomized groups of 30 patients. Patients who will have unusable data will be excluded from the analyses and replaced with a maximum total inclusion of 68 patients.

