### 5.2. EXLUCSION CRITERIA

#### Patients

- Metastatic at the time of inclusion,
- History of kidney cancer,
- Single kidney at the time of inclusion,
- Absence of preoperative CT scan or poor quality CT scan not allowing reliable 3D modeling,
- Person subject to a legal protection measure (judicial safeguard, guardianship or curatorship),
- Difficulty understanding and expressing oneself in French.

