| Modeling virtual 3D-model (according to randomized arm)  |                            |                    | X               |                                |                      |            |                             |                  |
| Printing 3D-model (according to randomized arm)          |                            |                    | X               |                                |                      |            |                             |                  |
| Preoperative information according to randomized arm     |                            |                    |                 | X                              |                      |            |                             |                  |
| Surgery                                                  |                            |                    |                 |                                |                      | X          |                             |                  |
| ASSESSMENTS                                       |                            |                    |                 |                                |                      |            |                             |                  |
| HLSEU-Q16 questionnaire (health literacy)                |                            | X                  |                 |                                |                      |            | X                           |                  |
| Questionnaire (knowledge of disease and planned surgery) |                            | X                  |                 |                                | X                    |            |                             | X                |
| Questionnaire of satisfaction                            |                            |                    |                 |                                |                      |            |                             | X                |
| Semi-directive interview                                 |                            | X                  |                 |                                | X                    |            |                             | X                |
|                                                          |                            |                    |                 |                                |                      |            |                             |                  |

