### 9.2.2 PATIENTS INCLUDED IN THE ANALYSIS

Only patients and professionals who present at least one of the following conditions may be excluded from the analysis:

- Patients wrongly included due to unsigned consent;
- Patients or professionals wrongly included due to major eligibility criterion(s) not met;
- Patients or professionals who have withdrawn their consent.

This exclusion decision will be taken by the Scientific Council without the knowledge of the randomization group and the patient's progress after inclusion.

Apart from these exclusions, patients or professionals who have died, been lost to follow-up or have abandoned the research will all be included in the analysis.

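### Section 9.1 excludes and replaces patients with unusable data, which contradicts the closed exclusion list in 9.2.2 and the all-participants rule in 9.2.1

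*Protocol*

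**What the plan says.** Section 9.1 (Study size, Patients) sets the size pragmatically: "it was decided to build a study with 60 patients divided into 2 randomized groups of 30 patients". It then adds: "Patients who will have unusable data will be excluded from the analyses and replaced with a maximum total inclusion of 68 patients". It does not say what makes data unusable, who decides, when, or whether that person knows the arm.

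Section 9.2.2 begins: "Only patients and professionals who present at least one of the following conditions may be excluded from the analysis". The three conditions are unsigned consent, a major eligibility criterion not met, and withdrawn consent. On the procedure it says: "This exclusion decision will be taken by the Scientific Council without the knowledge of the randomization group and the patient's progress after inclusion". It closes with the rule for everyone else: "patients or professionals who have died, been lost to follow-up or have abandoned the research will all be included in the analysis".

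Section 9.2.1 has the main analysis use the data of all participants, grouped by the model actually presented, on available data. Section 9.2.4 has missing data counted for each variable, with reasons where possible.

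**The concern.** Sections 9.1 and 9.2.2 give opposite instructions for the same patient. Someone lost after the first interview must stay in under 9.2.2, but may be removed and replaced under 9.1 if the remaining data are judged unusable. Patients who are lost or who abandon are the likeliest to have such data, so the conflict falls on the group that 9.2.2 expressly protects.

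What is at stake is comparability of the randomised groups. Whether a patient's interviews or questionnaires are usable can only be judged once they exist, which is after allocation. If that judgement is related to what the patient would have scored, and falls more heavily on one arm, the groups analysed are no longer those that were randomised. Recruiting a replacement restores the count but not the comparison. The masked decision in 9.2.2 would guard against this, but it is attached to its own three grounds, and 9.1 does not refer to it.

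**Working it through.** **1. The passages side by side**

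| Question | 9.1 | 9.2.1 and 9.2.2 |
|---|---|---|
| May poor or missing data remove a patient? | Yes | No; only consent or eligibility grounds |
| Lost to follow-up or abandoned? | Removable if data are unusable | All included |
| Who decides? | Not stated | Scientific Council |
| Masked to arm and progress? | Not stated | Yes |
| Main analysis | Excludes and replaces | All participants, on available data |

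**2. Timing and openness.** Section 7.3.3 randomises immediately after the inclusion consultation. The first interview and questionnaires follow by T0 + 15 days (7.4.1), and the later ones come at T3 and T6. The table in 7.2 puts allocation and the first questionnaires in one T1 column, but on either reading T3 and T6 come after allocation. Section 4.2 describes two parallel open arms. The social-science team conducts the interviews (7.4.1, 7.4.3, 7.5), alone transcribes and codes them (11.3.2), and analyses the data (9.2.1).

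**3. How many patients.** 68 − 60 = 8, and 8/68 = 11.8%. The protocol gives no effect size behind the 60 and no attrition rate behind the 68, so there is no calculation to reproduce. For orientation, 60/(1 − 0.10) = 66.7, rounded up to 67, and 60/(1 − 8/68) = 68. The cap therefore fits a loss of about 10% to 12%, but that rate is an assumption.

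**4. Size of a possible bias (illustration only).** Assumptions: 68 randomised as 34 per arm, a normally distributed score with SD 1, no true difference, and a correlation ρ between unusability and a low score. Removing the m most unusable of n patients shifts that arm's mean by about ρ × φ(z)/(1 − p), where p = m/n and z = Φ⁻¹(p).

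- m = 8: p = 0.235, z = −0.722, φ(z) = 0.3075; 0.3075/0.765 = 0.402
- m = 6: p = 0.176, z = −0.929, φ(z) = 0.2591; 0.2591/0.824 = 0.315
- m = 2: p = 0.059, z = −1.565, φ(z) = 0.1173; 0.1173/0.941 = 0.125

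At ρ = 0.5:

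- 8 v 0 removed: 0.5 × 0.402 = 0.20 SD
- 6 v 2 removed: 0.5 × (0.315 − 0.125) = 0.095 SD
- 4 v 4 removed: the shifts cancel

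A simulation under the same assumptions (20,000 runs, two-sided t-test at 5%) agrees. Each cell shows bias in SD, then type I error:

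| Removed | ρ = 0 | ρ = 0.3 | ρ = 0.5 | ρ = 1 (limit) |
|---|---|---|---|---|
| 4 v 4 | 0.00; 5.2% | 0.00; 5.4% | 0.00; 5.7% | 0.00; 8.7% |
| 6 v 2 | 0.00; 5.3% | 0.06; 5.4% | 0.09; 7.3% | 0.19; 16.6% |
| 8 v 0 | 0.00; 5.0% | 0.12; 7.2% | 0.20; 12.1% | 0.39; 38.0% |

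With ρ = 0 or equal removals there is no bias in the difference. Bias needs removals that are both related to outcome and unequal between arms.

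**The case against.** The best defence is that this is mainly an anthropological study without a power-based size, whose main criterion is a qualitative account of patient experience (3.1). Replacing an interview that cannot be used has an obvious practical motive there. Replacement is capped at 8, the CONSORT diagram (9.3.1) and the missing-data counts (9.2.4) would make removals visible, and 9.2.1 and 9.2.2 already point the same way, so 9.1 is one outlying sentence. An analysis plan not shown here might also define unusable data.

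Much of this limits the size of the problem. SD shifts have no meaning for the qualitative criterion; they concern only the literacy, knowledge and satisfaction questionnaires. But the defence does not remove the conflict, which lies within the protocol's own text. The study is also a randomised comparison with between-group tests at 5% (9.2.3, 9.2.5, 9.3.4), and a flow diagram reports exclusions without undoing them.

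Three stronger readings are tempting and are not supported:

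- **That the comparison will be biased, or that the removals will be decided by people who know the arm.** Section 9.1 names no decision-maker, and nothing in the protocol shows that removals will track the outcome or differ by arm. The text fails to prevent this; it does not prescribe it.
- **That eligibility exclusions can arise only in the personalised arm.** The argument would be that "Absence of preoperative CT scan or poor quality CT scan not allowing reliable 3D modeling" is a non-inclusion criterion (5.2), that a patient-specific model is built only in that arm, and that 9.2.2 allows exclusion for "Patients or professionals wrongly included due to major eligibility criterion(s) not met". But 7.3.3 already has the investigator confirm all eligibility criteria before randomisation in both arms, and in the generic arm the surgeon must still judge tumour size and location to choose a model (6.2.2). That such a reason would unmask the Council is conjecture.
- **That all 8 replacements could be added to one arm.** Section 4.3 balances the groups 1:1, and 9.1 does not say that replacement is within arm.

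**Conclusion.** The contradiction is real and needs no assumption: 9.1 orders an exclusion that 9.2.2 forbids and that 9.2.1 does not accommodate. It covers at most 8 of 68 patients (11.8%). Because the judgement comes after randomisation in open arms, and 9.1 gives no definition, decision-maker or masking, the rule permits exclusions related to outcome and arm.

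The resulting bias is a possibility, not a demonstrated fact. At an assumed correlation of 0.5 it would be about 0.1 SD (6 v 2 removed) to 0.2 SD (8 v 0) on questionnaire scores. It is absent if removals are balanced or unrelated to outcome. The correlation and the splits are assumptions, since the documents give no figure for either. The text is wrong as written and should be settled before any patient's data are judged.

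**What to change.** In 9.1, delete the wording that excludes and replaces patients with unusable data. State that every randomised patient is analysed under 9.2.2 on available data, with incomplete data reported by arm. Further patients, up to the 68 already allowed, may be randomised, but without removing anyone already randomised.

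If the sponsor wants to keep a data-quality exclusion, it should be defined in advance, added to the list in 9.2.2 under the masked Council decision, and reported by arm. A sensitivity analysis should then include the excluded patients.

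The cost is a wording change. The downside is that complete cases may end slightly below 30 per arm.

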### Patients

- Interventional study, prospective randomized, in 2 parallel open arms: one having a preoperative visit with a personalized 3D printed kidney model, the other with a generic 3D printed kidney model,
- Prospective inclusion.

Patients will be randomized with a 1:1 ratio to two groups:

- Group 1: Personalized 3D printed model group,
- Group 2: Generic 3D printed model group.

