### 4.3. RANDOMISATION METHOD

The randomization list is established by the statistician of the Methodology Center (USMR of the Bordeaux University Hospital) before the start of the research.

The numbers of the 2 strategy groups are balanced with a 1:1 ratio, without stratification factor. A document describing the randomization procedure is kept confidentially within the Methodology and Data Management Center.

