## 9.2 STATISTICAL METHODS USED

### 9.2.1 ANALYSIS STRATEGY

The data will be analyzed by the SHS research team to ensure cross-analysis of qualitative and quantitative data.

The main analysis will be carried out by sub-treatment for patients, i.e. the data of all participants must be analyzed with regard to the 3D printed model actually administered, even if randomization has decided otherwise, on available data.

The diagram below presents the different phases of the mixed method research proposed here. Many collection tools are used in this study to be able to study the effects of using a personalized 3D printed kidney model versus a generic 3D printed kidney model as a mediation tool on the patient experience and their interactions with professionals. This triangulation approach (21) requires specific analyses of the data obtained from the different collection tools, associated with cross-interpretations to meet the different objectives.

A descriptive analysis will be performed globally and by 3D model group.

A comparison analysis between the randomization groups will be performed, systematically without adjustment and with adjustment on the initial prognostic factors whose distribution could be, despite randomization, unbalanced.

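### Section 9.1 excludes and replaces randomised patients with undefined unusable data, contrary to the closed exclusion list in 9.2.2 and the all-participants rule in 9.2.1

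*Protocol*

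**What the plan says.** Three parts of protocol section 9 bear on who is analysed.

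- **9.1 (study size, patients).** The target: "it was decided to build a study with 60 patients divided into 2 randomized groups of 30 patients". The exclusion rule follows: "Patients who will have unusable data will be excluded from the analyses and replaced with a maximum total inclusion of 68 patients". The section does not define unusable, name who decides, or require masking for this step.
- **9.2.1 (analysis strategy).** For the main analysis, "the data of all participants must be analyzed with regard to the 3D printed model actually administered", using available data.
- **9.2.2 (patients included in the analysis).** The list is closed: "Only patients and professionals who present at least one of the following conditions may be excluded from the analysis". The conditions are missing consent signature, failure of a major eligibility criterion, and withdrawal of consent. On the procedure: "This exclusion decision will be taken by the Scientific Council without the knowledge of the randomization group and the patient's progress after inclusion". On everyone else: "patients or professionals who have died, been lost to follow-up or have abandoned the research will all be included in the analysis".

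The design sections give the context. Section 4.2 describes the patient part as "Interventional study, prospective randomized, in 2 parallel open arms". Section 4.3 says of allocation: "The numbers of the 2 strategy groups are balanced with a 1:1 ratio, without stratification factor". Section 7.3.3 places randomisation directly after the inclusion consultation and shows the result to the investigator at once.

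**The concern.** Unusable data is not among the three reasons in 9.2.2, so 9.1 removes patients whom 9.2.2 and 9.2.1 keep. The patients most likely to leave gaps (deaths, losses, dropouts) are the ones 9.2.2 names as retained. A statistical analysis plan that followed one section would breach the other, so this is not a detail that can be left to that document.

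The 9.1 rule is also the less safe of the two. Whether data are usable can be known only after they are collected, hence after randomisation. If exclusions differ by arm and are related to the outcome, the arms are no longer comparable as randomised. The number analysed is also unclear: 60 after replacement under 9.1, or everyone included (up to 68) under 9.2.2.

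**Working it through.** **1. The rules side by side**

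| Patient | 9.1 | 9.2.2 | 9.2.1 |
|---|---|---|---|
| No signed consent, major ineligibility, or consent withdrawn | not addressed | may be excluded, masked Council decision | not addressed |
| Died, lost or dropped out, data judged unusable | excluded and replaced | included | included on available data |
| Completed follow-up, data judged unusable | excluded and replaced | not on the list, so kept | included on available data |

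The second and third rows conflict.

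**2. When usability can be judged.** Randomisation comes right after inclusion (7.3.3). The first interview and questionnaires come at T1 (7.4.1), later ones at T3 and T6. A judgement on data quality therefore always uses post-randomisation information. The Council decision in 9.2.2 must be taken in ignorance both of the arm and of how the patient fared after inclusion. Even if it were extended to 9.1, the second condition could hardly be met.

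**3. Size of the group.** Maximum replacements: 68 − 60 = 8. Share of inclusions: 8/68 = 11.8%. The protocol gives no dropout rate or power calculation, so 68 cannot be reproduced from stated inputs. Back-solved, 60/(1 − 0.118) = 68. A 10% allowance would give 60/0.90 = 66.7, so 67. The figure fits an unstated allowance of roughly 10 to 12%.

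**4. Possible bias in the questionnaire comparisons.** Assumptions, none from the protocol: no true arm effect; 34 randomised per arm (68/2); normal outcome with SD 1; a latent usability score with correlation ρ to the outcome; the k lowest-scoring patients in an arm excluded; Student test at two-sided 5%; 8,000 replicates. Cells show the mean spurious difference in SD and the rejection rate.

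| ρ | 4/4 split | 6/2 split | 8/0 split |
|---|---|---|---|
| 0.3 | 0.00; 5.6% | 0.06; 5.3% | 0.12; 7.8% |
| 0.5 | 0.00; 5.8% | 0.10; 7.4% | 0.20; 12.2% |
| 0.7 | 0.00; 6.5% | 0.13; 9.6% | 0.28; 20.6% |
| 1.0 | 0.00; 8.4% | 0.19; 16.8% | 0.39; 37.6% |

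Closed-form check: removing the lowest fraction q of an arm shifts its mean by about ρ·φ(z_q)/(1 − q), where z_q is the normal quantile at q.

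- k = 8: q = 8/34 = 0.235, φ = 0.308, shift = 0.308/0.765 = 0.40ρ.
- k = 6: q = 6/34 = 0.176, φ = 0.259, shift = 0.259/0.824 = 0.31ρ.
- k = 2: q = 2/34 = 0.059, φ = 0.117, shift = 0.117/0.941 = 0.12ρ.

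The 8/0 difference is then about 0.40ρ and the 6/2 difference about (0.31 − 0.12)ρ = 0.19ρ, in line with the simulation.

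For scale, 30 per arm has 80% power for (1.96 + 0.84) × √(2/30) = 0.72 SD.

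**The case against.** - **The rules might be reconcilable.** Unusable could be shorthand for data that may not be used, which is the 9.2.2 list, or for patients with no data at all, who add nothing to an available-data analysis. Either is possible. Neither is written, and the second would still drop patients whom 9.2.2 says are included. The need to reconcile the sections stands.
- **The masked Council might be meant to cover every exclusion.** It is the only exclusion procedure in the protocol, but its wording ties it to the preceding list. A reader might go further and infer that unmasked staff will pick the analysis set, since the arms are open and the social-science team codes and analyses the interviews. The protocol does not say this; 9.1 names nobody.
- **A reader might infer that poorly verbal or low-literacy patients will be removed.** That is possible in an interview study but not stated. Section 5.2 already excludes people who have difficulty with French, and 9.2.4 reports missing questionnaire data per variable with reasons, so gaps alone are not treated as grounds for removal.
- **A reader might infer that replacements go to the depleted arm and so have predictable allocation.** Nothing supports this. Sections 4.3 and 7.3.3 describe a list prepared beforehand and allocation through the web interface.
- **Exclusions would be visible.** Section 9.3.1 plans a CONSORT flow diagram, deviations and visit counts. This makes them reportable but does not settle who is analysed.
- **The study is mainly qualitative.** The main criterion has no test attached, so the bias figures apply only to the questionnaire comparisons. This stands and limits the severity.

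**Conclusion.** The contradiction is real and rests on the text alone. Section 9.1 excludes on an undefined, post-randomisation criterion; 9.2.2 and 9.2.1 do not permit it, and the masked safeguard as worded does not reach it. At most 8 of 68 patients (11.8%) are affected.

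Harm to the comparison is conditional. Even exclusions cause no between-arm bias. Uneven ones could shift questionnaire comparisons by about 0.06 to 0.19 SD (6/2) or about 0.1 to 0.4 SD (8/0), given the assumed correlations of 0.3 to 1.0 and 34 patients per arm. The 8/0 split is the extreme case, and ρ = 1.0 equates usability with the outcome. These are illustrations of what the rule allows, not forecasts.

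Severity: should-fix.

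**What to change.** Delete the exclusion clause from 9.1 and let 9.2.2 alone define the analysis set, with every other randomised patient kept on available data. If the sponsor wants 60 patients with complete data, let inclusions 61 to 68 be additional patients who take the next places on a 68-place randomisation list prepared in advance. They are not replacements, and earlier patients stay in. Report patients with missing or incomplete data by arm, with reasons.

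The cost is about one sentence in 9.1 and a list of 68 places. No patients are needed beyond the stated maximum, and no power calculation has to be redone because none is given. The downside is a few patients with partial or no data in the tables. The change does not by itself secure a comparison as randomised, because 9.2.1 groups patients by the model they actually received.
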